### Sample size justification and planned data analysis strategy

Assuming as analysis method a RM-ANOVA with the within-subject variable time (before and after intervention [baseline, week 8]) and the between-group variable group (“add-on Celecoxib” versus “add-on placebo”) with *f* = 0.285 and a significance level of *α* = 0.05, a power of 1—*β* = 0.8 and a correlation between the measurements of *r* = 0.5, we calculated that we would need 38 patients (completers) per group (76 in total) to detect differences between groups (G*Power 3.1.9 was used for sample size calculation (Faul et al. 2007)). As we will perform an ITT analysis (linear mixed model analysis, if normality and variance homogeneity assumptions will be fulfilled), 76 patients is the aspired count of patients with 8-week primary endpoint data. Assuming a drop-out rate of 30%, 109 patients (76/0.7 ≈ 109) will have to be randomized. Based on preliminary data showing that 55% of patients with schizophrenia exhibit an inflammatory profile ([name]’ laboratory), we have calculated that (109/0.55 ≈ 199) should be screened. If the distribution of inflamed/non-inflamed participants does not follow this assumption, more patients will need to be screened to reach the inclusion of 109 patients with an inflamed profile. The intention-to-treat (ITT) population includes all patients with an inflamed profile who received at least one dose of IMP. The per protocol (PP) population will include all participants evaluable for the primary endpoint without major protocol violations. The safety population (SP) consists of all patients who entered the trial and will be used for conducting all safety analyses (in accordance with the ITT population).

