A statistical analysis plan will be developed before any analyses will be performed. For the primary endpoint analysis, a linear mixed model non-restrictively assuming an unstructured covariance matrix will be performed with fixed factors group, time and ‘group x time’ interactions. Analyses will be adjusted for centre, BMI, age and gender as obesity, age and gender may impact cytokine levels. Moreoever, an adjustment of those analyses for PANSS total baseline scores in the case of significant group differences will be performed. Baseline differences will be analyses with independent *t* test or Mann–Whitney *U* test. Continuous secondary endpoints will be analysed using linear mixed models adjusted for centre, age, BMI, gender and, if necessary, for related baseline values and with subsequent parametric post-hoc tests if the requirements for this strategy are met (tested by Kolmogorov–Smirnov tests and Levene’s tests). In cases where the assumptions of normality or variance homogeneity are violated, a monotonic continuous variable transformation will be performed. If this first step is not successful, corresponding non-parametric tests will be used. Additionally, binary logistic regression analysis including a factor variable for centres will be performed. Side-effects, AE and SAE will be analysed with descriptive statistics and likelihood-ratio tests. Demographic information will be shown for each group separately. Dichotomous variables will be analysed with likelihood-ratio tests and continuous variables will be analysed using analyses of variance or respective non-parametric tests. All tests of secondary endpoints will be computed in the ITT and per protocol (PP) populations in an explorative manner on a two-sided significance level of 5%. Outcome data of inflamed patients who participated in the double-blind treatment phase will be compared to the outcome data of the non-inflamed patients (naturalistic control group) in an exploratory manner. An interim analysis is not planned.

The primary economic evaluation (add-on study) will be in the form of a within-trial incremental cost–utility analysis appended with further cost-effectiveness analyses conducted both from a health and social care perspective and from a societal perspective (Drummond et al. 2005). All health economic analyses will be based on the ITT sample with multiple imputation of missing data together with extensive sensitivity and uncertainty analyses.

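### Likelihood-ratio tests are fixed for adverse events with no low-count alternative; at about 55 patients per arm they are anti-conservative for events with a true rate of roughly 2% to 10%

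*Protocol article*

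**What the plan says.** Under the heading on sample size justification and planned data analysis strategy, the protocol article fixes the safety method: "Side-effects, AE and SAE will be analysed with descriptive statistics and likelihood-ratio tests". Shortly afterwards it says: "Dichotomous variables will be analysed with likelihood-ratio tests". For continuous outcomes the same section sets out an assumption check, then a transformation, then a non-parametric test. It names no such fallback for binary outcomes with few events.

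On size, the article states that "109 patients (76/0.7 ≈ 109) will have to be randomized", starting from 38 completers per group. It sets a two-sided 5% level for secondary endpoints, which are tested in an explorative manner, and states no separate level for the safety tests. It does not say whether the likelihood-ratio p-value is asymptotic or exact. It gives no expected rate for adverse events or serious adverse events. The discussion cites only a rate below 1/10,000 for serious adverse reactions to the drug. An analysis plan is still to be written.

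**The concern.** The p-value of a likelihood-ratio test normally comes from a chi-square approximation, which needs reasonably large expected counts. With about 55 patients per arm, an individual event term seen in a handful of patients does not meet that condition. For some small totals the statistic is then too large, and an ordinary chance split is reported as p < 0.05.

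The error can run either way. Three events on celecoxib and none on placebo would read as a harm signal, and the reverse as apparent protection. Safety is a stated aim of the trial, and the test is named outright, so an analysis plan that follows the text would carry the problem forward.

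**Working it through.** **Inputs.** From the article: 109 randomized, two arms, 38 completers per group. Assumed: 1:1 allocation (55 and 54), asymptotic p-values, a two-sided 5% level for safety tests, and true event rates varied from 0.5% to 50% because none is given.

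**The plan's own figure.** With f = 0.285, a correlation of 0.5 and two measurements, the between-groups repeated-measures formula has noncentrality λ = f² × N × 2/(1 + 0.5). At N = 76, λ = 0.285² × 76 × 2/1.5 = 8.23 and power is 0.808; at N = 74 power is 0.798. So 76 is reproduced, and 76/0.7 = 108.6, rounded up to 109.

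**One table: 3 of 55 against 0 of 54.** The statistic is G = 2 Σ O ln(O/E), and the empty cell contributes nothing. Expected events are 55 × 3/109 = 1.514 and 54 × 3/109 = 1.486; expected non-events are 53.486 and 52.514.

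G = 2[3 ln(3/1.514) + 52 ln(52/53.486) + 54 ln(54/52.514)] = 2[2.052 − 1.465 + 1.507] = 4.19, so p = 0.041 on 1 degree of freedom.

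For 0 against 3, p = 0.038. Fisher's test gives 0.243 and 0.118; Pearson's chi-square gives 0.082 and 0.076.

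**Given the total number of affected patients.** With three affected in all, the likelihood-ratio test rejects whenever all three fall in one arm. Under no difference that has probability [C(55,3) + C(54,3)]/C(109,3) = (26,235 + 24,804)/209,934 = 24.3%. All totals from 1 to 10:

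| Patients affected | Likelihood ratio | Fisher |
|---|---|---|
| 1 or 2 | 0% | 0% |
| 3 | 24.3% | 0% |
| 4 | 11.8% | 0% |
| 5 | 5.7% | 2.7% |
| 6 | 2.7% | 2.7% |
| 7 | 11.3% | 1.3% |
| 8 | 6.0% | 3.2% |
| 9 | 3.2% | 3.2% |
| 10 | 9.3% | 1.6% |

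The excess is uneven: marked at 3, 4, 7 and 10, and small or absent at the other totals.

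**Over all totals.** Type I error at a common true rate p is Σ Bin(a; 55, p) × Bin(b; 54, p), summed over all tables (a, b) with a p-value below 0.05.

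| True rate | Expected patients (109p) | Likelihood ratio | Pearson | Fisher |
|---|---|---|---|---|
| 0.5% | 0.5 | 0.4% | 0.0% | 0.0% |
| 1% | 1.1 | 2.0% | 0.3% | 0.0% |
| 2% | 2.2 | 6.4% | 1.6% | 0.2% |
| 3% | 3.3 | 8.9% | 3.3% | 0.6% |
| 4% | 4.4 | 9.2% | 4.5% | 1.1% |
| 5% | 5.5 | 8.5% | 5.1% | 1.6% |
| 7% | 7.6 | 7.0% | 5.4% | 2.3% |
| 10% | 10.9 | 5.9% | 5.4% | 2.9% |
| 12% | 13.1 | 5.5% | 5.3% | 3.1% |
| 20% | 21.8 | 5.2% | 4.9% | 3.6% |

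The likelihood-ratio maximum is 9.3%, at a rate of 3.7%. It exceeds 6% for rates of about 2% to 9.5% and falls below 5% under about 1.7%. Pearson never exceeds 5.5% and Fisher never exceeds 4.0%, so the excess comes from the chosen test and not from small numbers alone. If only the 38 completers per arm were analysed, the likelihood-ratio maximum would be 9.1%.

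**Mid-P.** Taken as Fisher's p minus half the probability of the observed table, its error is 2.2% to 4.0% at rates of 3% to 5%. Taken as twice the one-sided mid-P, it is 1.0% to 2.4%. Either way the maximum is 5.5%.

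**The case against.** A reader might infer that the planned test is badly anti-conservative for adverse events as a whole. The article does not support that. Common events are tested at close to the nominal level and very rare ones conservatively. The only rate it cites, below 1/10,000, lies in the conservative range. That figure does not settle the matter, though: it concerns serious reactions to the drug, not adverse events of any cause in this population. Nor does the article say whether each event term will be tested or only the occurrence of any event, which might well be common. That sparse counts will dominate is therefore an assumption.

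A reader might also quote only totals of 3, 4, 7 and 10 affected patients and conclude that inflation is steady. The totals in between show that it is not.

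It can fairly be said that the choice of asymptotic or exact p-values belongs to the analysis plan, that the tests stand beside descriptive statistics, and that an independent safety monitoring board, not these p-values, watches over patients. This lowers the weight of the point but does not remove it. The article names a specific test and gives a fallback for continuous data only, and descriptive statistics do not correct a misleading p-value printed next to them.

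The objection that Fisher's test gives up sensitivity to real harm also stands: its error of 0.6% to 1.6% at rates of 3% to 5% is far below 5%. This is why Fisher alone is not the best remedy.

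**Conclusion.** The point holds within limits and is minor. If asymptotic p-values are used at a two-sided 5% level with arms of about 55 and 54, the named test has a true error of about 6% to 9% for events with rates of roughly 2% to 10%, that is, about 2 to 11 affected patients in the trial. Outside that band it is near nominal or conservative.

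How many event terms fall in the band cannot be derived from the article. As an illustration only, 20 independent terms, each with a true rate of 3% and no treatment effect, would yield about 20 × 0.089 = 1.8 nominally significant results by likelihood ratio, against 20 × 0.006 = 0.1 by Fisher.

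No confirmatory safety hypothesis rests on these tests, and the primary PANSS comparison is untouched.

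**What to change.** Add one sentence to the analysis section and carry it into the analysis plan: for adverse events, serious adverse events and other dichotomous variables with low counts, the likelihood-ratio test is replaced by a mid-P or exact test (Fisher or unconditional), and risk differences with score or exact 95% confidence intervals are the main safety summary. State the count below which the rule applies and, if mid-P is chosen, which two-sided definition is meant, since the two above differ at low rates.

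The cost is small. Standard software covers these methods, the analysis plan is not yet written, and six participants had been enrolled when the article was submitted. The downside is some conservatism, largest with Fisher's test. Making the intervals the main summary limits that loss, because they show how large a harm the data cannot exclude.

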### Organizational framework

Organizational project management, safety management, monitoring and data management is performed by the Münchner Studienzentrum (MSZ), an academic clinical research organization of the Technical University of Munich, School of Medicine. A detailed description of this framework is available elsewhere (Hasan et al. 2020). For safety monitoring, an independent safety monitoring board (SMB) with a SMB Charta has been established. The documentation of the study data in adherence to the GCP-guidelines and the clinical trial protocol is the responsibility of the investigator and will be performed in a certified clinical trial database (Macro 6). Original data (source documents) remain in hospital medical records and information on the case report form must be traceable and consistent with the original data. Original written informed consent signed by the patient is kept by the investigator and a signed copy will be given to the patient. All study procedures are in accordance with the guidelines of Good Clinical Practice (GCP) of the international conference on harmonization of technical requirements for registration of pharmaceuticals for human use (ICH), and the principles of the Declaration of Helsinki. All sites agreed to adhere to the instructions and procedures described in the study protocol and thereby to adhere to the principles of ICH-GCP. The most recent version of the study protocol is available at http://www.drks.de/DRKS00029044.

At the time of this article submission, the clinical trial is open for recruitment, which began late July 2022. Until now, six participants have been enrolled.

## Discussion

TargetFlame combines a precision psychiatry and a drug repurposing approach in which patients with an inflammatory phenotype are selected and treated with an immunomodulatory drug. The immune hypothesis of schizophrenia (Muller 2016; Bishop et al. 2022) poses one promising alternative to the classic dopamine hypothesis of schizophrenia. This concept allows to investigate therapeutic approaches beyond established pathways targeted by antipsychotics. Personalized medicine is already becoming a reality in cancer therapy where molecular diagnosis is leading more and more to tailored treatments with improved outcomes. In contrast to other medical specialties, diagnosis and prognosis in psychiatry are despite interesting approaches [e.g. multimodal machine learning outcome prediction (Koutsouleris et al. 2021)] still limited to the assessment of subjective and observable symptoms. Regarding concepts using multimodal data-integration, our approach in schizophrenia is based on a simple blood test, which could be, if successful, performed by many laboratories. Our project builds upon solid data indicating that immune-related biomarkers, and especially markers of inflammation, could be used as predictors for treatment response in psychosis patients (Martinuzzi et al. 2019) and that schizophrenia patients could readily be stratified into two clinically distinct clusters based on serum levels of several pro-inflammatory cytokines. A meta-analysis performed by members of our group showed that the general concept of repurposing anti-inflammatory drugs in addition to an antipsychotic treatment is of interest. This meta-analysis identified a total of 70 randomized controlled trials with 4104 participants and showed that adding an anti-inflammatory agent to antipsychotic treatment was superior to adding placebo (SMD = − 0.29; 95% CI = − 0.40 to − 0.19). However, the results for the established NSAIDs that have the potential to be repurposed for a broad use in clinical practice due to our long-standing experience with those compounds showed heterogenous results (Jeppesen et al. 2020). An analysis of the efficacy of repurposing NSAIDs (ASS, Celecoxib) based on five studies and 138 (active compound) vs. 124 (placebo) patients showed a relevant between-study heterogeneity and no overall effect (95% CI = − 11.43 to 3.25) (Jeppesen et al. 2020). Thus, there is an urgent need for tailored treatment approaches focusing on those patients who show relevant peripheral inflammation rather than adding a NSAID to every patient with schizophrenia with ongoing symptoms.

Using Celecoxib for the proposed indication demands a detailed risk–benefit evaluation. Celecoxib has been approved and is indicated according to the *Summary of product characteristics* (SmPC) for treatment of osteoarthritis, rheumatoid arthritis, juvenile rheumatoid arthritis in patients 2 years and older, ankylosing spondylitis, acute pain and primary dysmenorrhea. TargetFlame will repurpose Celecoxib for the treatment of schizophrenia. Patients will be treated with their usual antipsychotics with additional health monitoring through multiple clinical examinations as well as blood tests and electrocardiogram (ECG) that go beyond the safety assessment in clinical practice. Using an IMP such as Celecoxib may be associated with drug-specific side effects, which will be assessed through collection of safety parameters. Of note, Celecoxib has a favourable side effect profile with serious adverse reactions being very rare according to the Summary of Product Characteristics (< 1/10,000). Additionally, and in contrast to newly developed and untested molecules, Celecoxib has been used for many years in other indications and long-term dosage of 400 mg per day, thus offering the advantage of having been extensively tested in large study populations. Since Celecoxib is almost exclusively metabolized through the liver and excreted in the form of inactive metabolites via the faeces and the kidneys, tests of liver and kidney function will be performed. Broad exclusion criteria focussing on the main risks associated with Celecoxib such as cardiovascular event, gastrointestinal or hematologic side-effects have been implemented. The cardiovascular safety of Celecoxib was shown to be not inferior to other NSAIDs (Nissen et al. 2016). Moreover, most risks are associated with a long-term use of Celecoxib, and we will apply the IMP for a maximum of eight weeks. Our precision psychiatry approach will further reduce the individual risk as only those patients who have an inflammatory profile will be included. Until now, studies using anti-inflammatory drugs to treat schizophrenia (e.g. Celecoxib, ASS, *N*-acetylcysteine, the antibiotic minocycline, the neurosteroid pregnenolone or Dehydroepiandrosterone (DHEA), or monoclonal antibodies such as tocilizumab) [for review see (Jeppesen et al. 2020)] did not stratify according to an individual phenotype. Such approach is also expected to improve cost-effectiveness.

## Conclusions

The goal of the Target Flame trial was to evaluate the effects of an add-on treatment with the anti-inflammatory drug Celecoxib in a subset of schizophrenia patients exhibiting an inflammatory profile. To this aim, we will conduct an exploratory randomized, double-blind phase III clinical trial in prospectively recruited patients with schizophrenia spectrum disorders. Inflamed patients will be randomized in two arms and treated with either add-on Celecoxib or add-on placebo. Clinical assessments and health economic assessments will be performed at baseline and after 2 months (end of intervention) and 6 months (follow-up). TargetFlame is the first trial in schizophrenia research combining stratified treatment and drug repurposing approaches.

## Data Availability

Data sharing not applicable to this article as no datasets were generated or analysed during the current study.
